| Study implementation | Adolescents with type 1 diabetes whose current glycated haemoglobin level is greater than or equal to 8.5% are included and randomised to two groups, then followed up for 6 months:   - patients with standard follow-up (G1), - patients with standard follow-up and receiving text messages (SMS) (G2).   V0- Inclusion visit   - Verification of eligibility criteria - Invitation to take part in the study. - Collection of the non-objection form for participation in a cohort on compliance (IL1) - Randomisation. - Only adolescents randomised to group G2 are informed that they will receive text messages (SMS) (Zelen method). - Collection of the non-objection form for participation in the text messaging (SMS) study if the patient is randomised to the investigational arm (IL2) - Inclusion - Clinical examination - Blood sample: assay of HbA1c level - Completion of quality of life questionnaire - Completion of inclusion form   M3 – 3-month visit   - Clinical examination - Blood samples for laboratory work-up (assay of HbA1c level) - Completion of M3 follow-up form - Completion of quality of life questionnaire - Collection of blood glucose monitoring diary and distribution of a second diary   M6 – 6-month visit:   - Clinical examination - Blood samples for laboratory work-up (assay of HbA1c level) - Completion of M6 follow-up form. - Collection of capillary blood glucose diary distributed at M3. - Completion of quality of life questionnaire - Satisfaction survey for patients randomised to the text messaging arm   Text messaging characteristics:   - A text message will be sent every day. - At the usual insulin injection times based on the patient’s personal therapeutic regimen. - Example of message content:   *“Remember to administer your slow-acting insulin injection.”*  *“You are about to have your meal; remember to administer your rapid-acting insulin injection (or bolus - if a pump is used).”*  *“Remember to administer your mixed insulin injection.”* |
| Primary and secondary endpoints | Primary endpoint   - HbA1c level at 6 months   Secondary endpoints   - HbA1c level at 3 months - Measurement of compliance at M3 and M6: blood glucose monitoring diary - Inclusion, M3 and M6 quality of life questionnaire. - Satisfaction survey for patients randomised to the text messaging arm |

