| Statistical analysis | Analysis of the primary endpoint: comparison of HbA1c level at 6 months between patients having received text messages and patients not having received reminder text messages.  Analysis of the secondary endpoints: comparison of HbA1c level at 3 months, compliance and quality of life between patients having received text messages and patients not having received reminder text messages, analysis of the satisfaction survey. |

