# **GENERAL STUDY FLOW CHART**

Inclusion visit

Non-objection to participation in a 6-month cohort study

Randomisation

Control arm G1:

Standard management

Investigational arm G2:

Daily text messaging

Non-objection

to receiving text messages

Objection

Non-objection

Standard management

Text messaging

Assessment at 3 months and 6 months

|  | V0 | M3 | M6 |
| --- | --- | --- | --- |
| Verification of eligibility | X |  |  |
| Information | X |  |  |
| Non-objection to participation in a cohort study | X |  |  |
| Randomisation | X |  |  |
| Non-objection to receiving texts for adolescents in group G2 | X |  |  |
| Clinical examination | X | X | X |
| Clinical form to be completed | X | X | X |
| Laboratory work-up (HbA1c) | X | X | X |
| Distribution of blood glucose monitoring diary | X | X |  |
| Collection of blood glucose monitoring diary |  | X | X |
| Quality of life questionnaire | X | X | X |
| Satisfaction survey (only for patients in the text messaging arm) |  |  | X |

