## SECONDARY OBJECTIVES

The secondary objectives fall into four categories.

Firstly, we will assess HbA1c level after 3 months of follow-up.

Secondly, we will measure compliance via the blood glucose diary at 3 months and 6 months after the start of the study. This diary is given to the patient at the start of the study, then at the 3-month study visit. Thirdly, we would like to assess quality of life among adolescents based on a questionnaire given to the patients at inclusion, at 3 months and 6 months after the start of the study (PedsQL questionnaire version 4.0). Lastly, we would like to conduct a satisfaction survey alongside adolescents randomised to the text messaging arm at 6 months of participation in the study.

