## Summary table of the study time-line

|  | Inclusion | M3 | M6 |
| --- | --- | --- | --- |
| Eligibility | X |  |  |
| Information | X |  |  |
| Non-objection | X |  |  |
| Randomisation | X |  |  |
| Clinical form to be completed | X | X | X |
| Clinical examination | X | X | X |
| Assay of HbA1c level | X | X | X |
| Distribution of blood glucose monitoring diary | X | X |  |
| Text message sent | X | X | X |
| Collection of blood glucose diary |  | X | X |
| Quality of life questionnaire | X | X | X |
| Satisfaction survey (text messaging arm) |  |  | X |

Table 2: Summary table of the study time-line

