## Description of planned statistical methods, including the planned interim analysis schedule

The statistical analysis will be carried out using SAS software, under the supervision of [name] (Paris Centre CRU - Cochin-Necker). The statistical analysis will be carried out at the end of data collection, data entry and data consistency checks.

A descriptive analysis of the characteristics of the children included in each group will be performed first of all. Quantitative data are expressed as the mean ± standard deviation or median and range, and as the sample size and percentage for qualitative data.

The primary endpoint and secondary endpoints will be analysed on an intention-to-treat basis, i.e. all randomised patients will be analysed in their randomisation arm, irrespective of the intervention received. All tests used will be two-sided, with a 5% significance level.

*Main analysis*

The HbA1c level after the 6-month follow-up period will be compared between the “text messaging” and control groups using Student’s *t*-test.

*Secondary analyses*

The HbA1c level after the 3-month follow-up period will be compared between the “text messaging” and control groups using Student’s *t*-test.

For all secondary endpoints, satisfaction and compliance, two means will be compared using Student’s *t*-test or a Wilcoxon test if necessary. The percentages will be compared using the Pearson Chi-2 test or Fisher’s exact method, if necessary.

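### Section 12.2 prescribes a two-group test of satisfaction, which is surveyed in the text-messaging arm only; it also leaves quality of life unnamed and its inclusion score unused

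*Protocol*

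**What the plan says.** Section 12.2 (Secondary analyses) first plans a t-test for HbA1c at 3 months. It then states: "For all secondary endpoints, satisfaction and compliance, two means will be compared using" Student's t-test, or a Wilcoxon test if needed. For categorical results it adds: "The percentages will be compared using the Pearson Chi-2 test or Fisher’s exact method, if necessary". The section also sets an intention-to-treat rule for primary and secondary endpoints alike, with every randomised patient kept in the assigned arm. The only two groups that the protocol defines are text messaging (G2) and control (G1).

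On who receives the satisfaction survey:

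- Section 2.3 (Secondary objectives) plans a "satisfaction survey alongside adolescents randomised to the text messaging arm at 6 months of participation in the study".
- The Synopsis lists it as "Satisfaction survey for patients randomised to the text messaging arm".
- The General study flow chart has "Satisfaction survey (only for patients in the text messaging arm"), marked at M6 only.
- Section 5.3 (Follow-up visits) and Table 2 restrict it in the same way.
- Section 4.5.2 lists it as a secondary endpoint without naming an arm.

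On quality of life, sections 2.3 and 4.5.2 make PedsQL 4.0 a secondary objective and endpoint, measured at inclusion, 3 months and 6 months. Sections 5.2 and 5.3 collect it from all patients. The statistical row of the Synopsis plans to compare HbA1c at 3 months, "compliance and quality of life between patients having received text messages" and those who did not receive them. It mentions the satisfaction survey separately, as something to be analysed.

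**The concern.** A two-mean comparison needs values in two groups, and for satisfaction the second group is empty by design. The gap could not be closed by surveying controls. Under the modified Zelen design only G2 patients are told about the texts, so a control patient has nothing to rate.

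An analyst who follows section 12.2 therefore meets a prespecified test that cannot be carried out, and a Synopsis that describes the analyses differently. The two places have to be reconciled.

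The same sentence deals badly with quality of life. Section 4.4.2 cites satisfaction and quality of life as the subjective endpoints that motivate the Zelen design. Of these two, only quality of life can be compared between arms, yet section 12.2 names the other. The planned t-test or Wilcoxon test also makes no use of the inclusion score, which the protocol already collects in both arms. What is at stake is the clarity of the secondary analyses and some precision for PedsQL.

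**Working it through.** **The plan's own figures.** The only related design figure is the sample size in section 12.1 (SD 1.6, difference 1, two-sided 5%, power 80%):

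n per group = 2 × (1.96 + 0.84)² × 1.6² / 1² ≈ 40.1, rounded up to 41. This agrees with the protocol.

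41 × 1.2 = 49.2, which the protocol sets at 50 per group.

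The point does not depend on this calculation. It only fixes the largest possible number of respondents.

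**Values available by arm**

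| Endpoint | G2 (texts) | G1 (control) | Time of collection |
|---|---|---|---|
| Satisfaction | at most 50 | 0 | M6 |
| PedsQL | at most 50 | at most 50 | inclusion, M3, M6 |
| Compliance (diary) | at most 50 | at most 50 | M3, M6 |

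**Satisfaction under each stated test**

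- t-test: the standard error is s × √(1/50 + 1/0), which is undefined. Running a two-sample t-test with 50 values against none returns no statistic, no degrees of freedom and no p-value.
- Wilcoxon: the number of between-group pairs is 50 × 0 = 0, so there is nothing to rank across groups.
- Chi-square or Fisher: one column of the table is empty, so no contrast exists.
- Before and after: the survey is given once, so there is no within-patient change either.

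**Section 12.2 against the Synopsis**

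| Endpoint | Section 12.2 | Synopsis, statistical row |
|---|---|---|
| Satisfaction | named for comparison of two means | analysed, not among the comparisons |
| Compliance | named for comparison of two means | compared between groups |
| Quality of life | not named; falls under all secondary endpoints | compared between groups |

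The Synopsis version can be carried out. The section 12.2 version cannot, for satisfaction.

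**Who is surveyed.** The Synopsis and section 5.3 address the survey to patients randomised to texting. Section 5.2 gives those who refuse texts conventional follow-up, and section 12.1 has those who withdraw consent followed as the control group is, which includes no survey. At the planned refusal of about 10%, 0.10 × 50 = 5 patients fall between the two readings. The number surveyed is up to 50 on one reading and up to 45 on the other. On both, the control count is 0.

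**PedsQL and its inclusion score.** With correlation ρ between inclusion and follow-up scores, ANCOVA multiplies the residual variance of the follow-up comparison by about (1 − ρ²), at the cost of one degree of freedom. The protocol gives no value for ρ, so I put no figure on the gain. Apart from that one degree of freedom, precision is no worse than with the unadjusted t-test.

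This holds if the inclusion score is a true baseline. Both the inclusion-visit list in the Synopsis and section 5.2 place the questionnaire after randomisation and after the second leaflet (IL2). A G2 patient may by then know about the texts, and adjusting for a score that allocation could already have moved can distort the comparison.

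**The case against.** The strongest case on the other side is that little harm can follow. With no control responses, the satisfaction test cannot be run by mistake and cannot give a wrong result. The Synopsis already treats the survey correctly, so this may be a drafting slip with satisfaction written in place of quality of life. Nothing about the primary endpoint, the error rate or the conduct of the trial is touched. All of that is fair and limits the weight of the point. It does not remove the conflict, because the methods section names an analysis that the design rules out.

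A reader might infer that the between-arm comparison of quality of life is missing. The documents do not support that. The sentence in section 12.2 opens with all secondary endpoints, section 4.5.2 lists quality of life among them, and the Synopsis plans the comparison outright. It is unnamed in section 12.2, not absent.

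A reader might also conclude that about 5 of 50 surveyed patients will be rating texts they never received. That is only one reading, because sections 5.2 and 12.1 can be taken to put refusers outside the survey.

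Finally, the unadjusted t-test or Wilcoxon test for PedsQL is valid, so ANCOVA is an improvement and not the repair of an error. That objection stands.

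**Conclusion.** The satisfaction analysis in section 12.2 is wrong as written: at most 50 values against 0, with no comparator at any time point, and in conflict with the Synopsis. This rests only on the data-collection schedule, which is consistent wherever an arm is named. It is more than a detail left to a statistical analysis plan, because the protocol states an analysis that its own design makes impossible.

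For quality of life the finding is narrower. Section 12.2 should name it, and its test should use the inclusion score. The size of that gain depends on a correlation the protocol does not give. The adjustment assumes that inclusion and follow-up questionnaires can be linked by patient; section 4.5.2 calls the questionnaire anonymous, which must mean coded for this to work.

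Whether refusers are surveyed is unclear and needs a decision. The documents do not support a claim that a set number of non-recipients will be surveyed. A reader may also be drawn to limit satisfaction to patients who received a text, or to fix a format such as exact intervals for proportions. The first departs from the section's intention-to-treat rule, and the second assumes a survey format that is not in the text at hand.

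The point is worth correcting but modest. The primary endpoint and sample size stand.

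**What to change.** Replace the sentence on secondary endpoints in section 12.2 with wording to this effect:

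> Satisfaction at M6 is described within the text-messaging arm only; no between-arm test is made. Compliance and PedsQL at M3 and M6 are compared between the randomised arms. PedsQL is analysed by ANCOVA with the inclusion score as covariate.

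Then make three small alignments:

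- State whether patients who refuse or withdraw from texting receive the survey, and make the Synopsis and sections 5.2, 5.3 and 12.1 agree.
- Take the list of compared endpoints from the Synopsis, but keep the intention-to-treat grouping of section 12.2. The Synopsis words the groups by receipt of texts.
- In section 5.2 and the Synopsis visit list, place the inclusion PedsQL before the arm is disclosed, and say that the questionnaires carry the patient code.

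The cost is one paragraph in section 12.2 and a few lines elsewhere. No new data, visits or patients are needed. The one practical burden is the order of steps at the inclusion visit, and the analysis gives up one degree of freedom.

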### Secondary endpoints

The secondary endpoints are as follows:

- Improvement in blood glucose control at 3 months
- Measurement of compliance: by assessing the capillary blood glucose diary, at 3 months and at the end of the study.
- Measurement of quality of life among the adolescents: anonymous self-administered questionnaire distributed, at inclusion, at 3 months and at the end of the study (PedsQL questionnaire version 4.0).
- Satisfaction survey after 6 months of participation in the study.

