## ASSESSMENT SCHEDULE FOR THE DIFFERENT GROUPS

The principal endpoint will be assessed at the inclusion visit and during the follow-up visits at 3 and 6 months. The secondary endpoints will be assessed at the follow-up visits at 3 and 6 months.

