## VISIT V1 - INCLUSION VISIT

The investigator will inform parents of potentially eligible minor patients and will invite their child to take part in the cohort study aiming to assess changes in diabetes control over a 6-month period (Information leaflet 1_ APPENDICES 8 and 9). Adult patients will be informed by the investigator directly.

Non-objection by the parents and/or adolescents will be documented in the patient’s medical record (date on which the information was provided, objection expressed or not, and signature of the person in charge of the visit).

Clinical examination

After verifying the eligibility criteria and non-objection to participation in the study, the investigator will collect the medical history and clinical information usually taken into account in the management of diabetic patients:

- medical history
- history of psychiatric disorders
- date of diabetes diagnosis
- current treatment regimen and insulin analogue injection times

Laboratory tests

Glycated haemoglobin (HbA1c) levels will be measured according to the method used at Centre Hospitalier de Necker.

Randomisation

- Patients randomised to the “text messaging” investigational arm: a second information leaflet (IL2- APPENDICES 10 and 11) on the study objectives and text messaging intervention procedures will be given to the parents and/or young patients. If patients refuse the text messaging intervention, the patients will receive conventional follow-up. Non-objection by the parents and/or adolescents to the text messaging intervention will also be documented in the patient’s medical record (date on which the information was provided, objection expressed or not, and signature of the person in charge of the visit).
- Patients randomised to the “standard management” control arm will receive their usual care.
- Completion of the quality of life questionnaire for all patients

At the end of the visit, the investigator will send the information sheet for centralised data entry.

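### Quality of life is collected at inclusion, but section 12.2 compares the arms without it; baseline adjustment would gain precision once the inclusion score is made pre-allocation and linkable

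*Protocol*

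**What the plan says.** **Collection.** Protocol section 2.3 describes a "questionnaire given to the patients at inclusion, at 3 months and 6 months after the start of the study (PedsQL questionnaire version 4.0"), the Synopsis lists "Inclusion, M3 and M6 quality of life questionnaire" among the secondary endpoints, and section 4.5.2 has the instrument "distributed, at inclusion, at 3 months and at the end of the study (PedsQL questionnaire version 4.0"). Section 5.2 includes, at the inclusion visit, "Completion of the quality of life questionnaire for all patients".

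**Comparison.** The Synopsis (Statistical analysis) plans a "comparison of HbA1c level at 3 months, compliance and quality of life between patients having received text messages" and those without, so quality of life is a between-arm endpoint.

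**Test.** Section 12.2 addresses its rule to all the secondary endpoints, naming satisfaction and compliance, and states that "two means will be compared using Student’s *t*-test or a Wilcoxon test if necessary". Quality of life is not named in that sentence. No covariate, change score or repeated-measures model is given for any endpoint.

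**Timing in section 5.1.** "The secondary endpoints will be assessed at the follow-up visits at 3 and 6 months". Inclusion is not mentioned there.

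**Order and identification of the inclusion questionnaire.** The Synopsis (V0) and section 5.2 both list it after randomisation and after the text-messaging arm has received the second leaflet (IL2). Section 4.5.2 calls the questionnaire anonymous. The M3 and M6 forms (Appendices 4 and 5) have an item for the quality of life questionnaire; the inclusion form (Appendix 3) has none.

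**The concern.** A patient's inclusion score usually carries information about the later score. A two-sample test on follow-up values leaves that predictable variation in the error term, and any chance difference between arms at inclusion stays in the estimate. The trial is sized on HbA1c alone (section 12.1), so quality of life gets whatever precision 50 per arm happens to provide. If the inclusion score is a usable baseline, the same patients and visits could give a narrower confidence interval, and a null quality of life result would be somewhat more informative.

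Section 12.2 is not silent here. It names a test, and an analysis plan that followed it would run that test unadjusted.

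**Working it through.** **Inputs from the protocol.** Two-sided 5% level (12.2); 41 per arm before inflation and 50 per arm after it (12.1); HbA1c SD 1.6 and difference 1% (12.1). No SD, target difference or power is given for the PedsQL.

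**Assumptions, not in the protocol.** ρ, the within-arm correlation between inclusion and follow-up PedsQL, taken from 0.3 to 0.7; a true difference of 0.5 SD, for illustration.

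**The protocol's own figure first.** n per arm = 2 × 1.6² × (1.960 + 0.842)² / 1² = 5.12 × 7.85 = 40.2, so 41. Then 41 × 1.20 = 49.2, so 50. Both reproduce. They concern HbA1c and say nothing about quality of life beyond fixing the number of patients.

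**Unadjusted comparison of follow-up scores, 50 per arm.** In SD units the noncentrality is 0.5 × √(50/2) = 2.50, with 98 degrees of freedom and critical value 1.984. Power is 69.7%. The difference detectable with 80% power is 0.566 SD.

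**ANCOVA on the inclusion score.** The residual SD is multiplied by √(1 − ρ²), so the noncentrality is 2.50 / √(1 − ρ²) with 97 degrees of freedom. The equivalent unadjusted size is 50 / (1 − ρ²) per arm.

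| ρ (assumed) | Variance reduction ρ² | Noncentrality | Power at 0.5 SD | Detectable at 80% power | Equivalent n per arm |
|---|---|---|---|---|---|
| unadjusted | 0 | 2.50 | 69.7% | 0.566 SD | 50 |
| 0.3 | 9% | 2.62 | 73.7% | 0.540 SD | 54.9 |
| 0.5 | 25% | 2.89 | 81.5% | 0.490 SD | 66.7 |
| 0.7 | 49% | 3.50 | 93.4% | 0.404 SD | 98.0 |

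The gains are 73.7 − 69.7 = 4.0 points, 81.5 − 69.7 = 11.8 points and 93.4 − 69.7 = 23.7 points. Below ρ = 0.3 the gain is smaller still.

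**Simulation check.** With 4,000 simulated trials per value of ρ, power was about 69% for the t-test and 73%, 82% and 94% for ANCOVA.

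**Fewer patients.** At 41 per arm, power is 60.9% unadjusted and 73.3% adjusted at ρ = 0.5, so the gain does not depend on reaching 50 per arm.

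**Change scores.** If the two means were read as mean changes from inclusion, the variance would be 2(1 − ρ) times that of the follow-up-only test: 1.4 times at ρ = 0.3, equal at 0.5, and 0.6 times at 0.7. ANCOVA's factor, 1 − ρ², is 0.91, 0.75 and 0.51, which is lower in each case.

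**The case against.** **The inclusion score is not a clean baseline as the visit is written.** This is the strongest objection, and it stands. The Synopsis and section 5.2 list the questionnaire after randomisation and after the messaging arm learns of the messages. That is the listed sequence for everyone, not an occasional lapse. Section 4.4.2 itself regards patient-reported endpoints as wholly subjective. If the news shifts answers in one arm, adjusting for that score could bias a comparison that is otherwise unbiased. A reader might infer that the precision is already in hand and needs only a change of test; the documents do not support that.

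**Linkage is not assured.** This also stands. ANCOVA needs each patient's inclusion score tied to the later ones. Section 4.5.2 calls the questionnaire anonymous, and Appendix 3 has no item for it.

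**The protocol does not clearly fix the quality of life analysis.** This stands in part. Quality of life comes in only through the reference to all secondary endpoints, and the wording does not strictly rule out change scores. But none is mentioned, section 5.1 points to follow-up values, and a change score would not match ANCOVA.

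**The planned test is not wrong.** Correct. A reader might infer that the comparison is biased, or that the lack of stratification leaves baseline quality of life unbalanced. Neither follows: randomisation balances it in expectation, and any chance imbalance is allowed for in the test's error rate.

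**Section 5.1 might be read as dropping the inclusion questionnaire.** It does not support that. Sections 2.3, 4.5.2 and 5.2, the Synopsis and the visit tables all keep it, so 5.1 is loose wording.

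**Conclusion.** The point holds as a low-priority efficiency improvement on a secondary endpoint. The stated t-test or Wilcoxon comparison is valid and unbiased, but it makes no use of an inclusion score that the protocol plans to collect from every patient.

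The size of the loss rests on ρ, which the protocol does not give, and on the illustrative 0.5 SD difference. It is modest at ρ = 0.3 or below and material from about 0.5 upwards. Even at ρ = 0.5 the detectable difference moves only from 0.57 to 0.49 SD, so the trial would still be informative only about moderate effects on quality of life.

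The gain is conditional: the inclusion score must be obtained before allocation is known and must be linkable to the patient. As written, neither is assured, so changing the test alone would not be a safe amendment.

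**What to change.** 1. **Synopsis (V0) and section 5.2:** place completion of the inclusion PedsQL before randomisation and before the IL2 information, so that it is a true pre-allocation baseline.
2. **Section 4.5.2 and Appendix 3:** replace the description of the questionnaire as anonymous with coded by patient number, and add a PedsQL item to the inclusion form.
3. **Section 12.2:** add, for example: *PedsQL total score at M3 and at M6 will be compared between randomised arms by analysis of covariance with the pre-allocation inclusion score as covariate; the adjusted mean difference and its 95% confidence interval will be reported.* Give a simple rule for missing inclusion scores, such as mean imputation of the covariate.
4. **Scores obtained after allocation was known:** do not use them as the covariate. If that is the general case, keep the unadjusted comparison as the main quality of life analysis.
5. **Section 5.1:** as a minor alignment, state that quality of life is also assessed at inclusion.

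The cost is a reordering of steps within one visit, coding of the questionnaires, one form item and a few sentences of text. No extra patients, visits or samples are needed.
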